### Study Design

In this multicenter, single-blinded RCT, we will examine the effectiveness of BITT compared to a WLCG. Participants will be recruited over 27 months (October 2022-December 2024). To determine the effectiveness of BITT, we will compare the outcomes of the BITT intervention group (n=50) with the outcomes of a WLCG (n=50). We will conduct assessments at similar time points for both groups: at baseline (T0), directly after BITT or WLCG (T1), and at 3 (T2), 6 (T3), and 9 (T4) months follow-up after the baseline measurement. The WLCG will receive BITT after the 3-month follow-up assessment. Figure 1 provides an overview of the study design.

**Figure 1 figure1:**
[figure not shown]
Flowchart of the randomized controlled trial design. BITT: Brief Intensive Trauma Treatment.

The treatment phase of BITT lasts only 1 week (ie, 5 consecutive workdays). The WLCG will not receive psychological care (ie, EMDR and TF-CBT) during this week. After this week, participants from the BITT group will follow regular follow-up care, which usually consists of EMDR and TF-CBT. Apart from BITT, the WLCG can receive any treatment including EMDR and TF-CBT, during this period. We will monitor and register all provided care in the research database (inclusion and exclusion criteria listed in Textbox 1).

Inclusion and exclusion criteria.Inclusion criteriaParticipants must meet all of the following criteria:12-18 years of age;A history of psychological trauma (as measured by the Life Events Checklist of the Clinician-Administered Posttraumatic Stress Disorder Scale for Children and Adolescents in the *DSM-5 [Diagnostic and Statistical Manual of Mental Disorders* (Fifth Edition)]) [35,36];At least subthreshold posttraumatic stress disorder criteria, conform to the Clinician-Administered PTSD Scale for Children and Adolescents *DSM-5*, that is:fully meets criteria A, F, and G, and at least one symptom of criteria B, C, D, and E;fully meets criteria A, F, G, and at least one of the B, C, D, or E symptom clusters;The adolescent must provide written informed consent. For adolescents aged 12-15 years, all legal guardians must also provide consent.Exclusion criteriaAdolescents who meet any of the following criteria will be excluded from participation in this study:inability to speak and write Dutch;estimated or determined intellectual disability (IQ <70);having ongoing trauma by a parent who is part of the adolescent’s current primary care system.

### Power Analyses

A power analysis in R (R Core Team) [37] (script available on request) showed that a sample size of n=66 (33 in the direct group and 33 in the WLCG) is sufficient to reach a required power of at least 80% when assuming Cohen *d*=0.5. Regarding trauma-focused therapies, we expected a dropout rate of around 25% [15-17], implying that we would need at least 88 (ie, 66 divided by 0.75) participants. To ensure sufficient statistical power, we aimed for a total sample size of 100. This sample size will also be sufficient when adding the covariates to the model.

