### Randomization

After obtaining written informed consent from participants, an independent researcher will randomize them to either the BITT group or WLCG using computerized block-wise randomization in Castor Electronic Data Capture [38]. We will use random block sizes to avoid predictability for the researchers and we will stratify by center. The researcher completing the assessments will be blinded to the group allocation (ie, BITT vs WLC). We will explicitly instruct participants not to communicate their group allocation to the researcher.

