### Statistical Analysis

We will conduct the analyses in consultation with a statistical expert. Data analyses will include the following:

We will define the effects of BITT in terms of group differences between the BITT and WLCG. These differences will be tested according to both the intention-to-treat-principle and completers’ analyses. That is, the pre, post, and follow-up changes (BITT vs WLCG) on the continuous outcomes (ie, trauma symptoms, anxiety symptoms, depression symptoms, anger symptoms, quality of life, and self-harm) will be tested with mixed models; dichotomous outcomes (ie, suicide attempts and dropout) with generalized estimating equation (GEE).Mixed models will also be used to investigate possible moderation effects, which concern effects of (1) age, gender, SES, type of trauma, number of traumatic events, comorbidity, caregivers’ PTSD, and treatment center on PTSD; and (2) residency (ie, urban and rural) and ethnicity on BITT dropout.The qualitative interviews about the experiences of adolescents, caregivers, and therapists with regard to BITT will be verbatim transcribed and analyzed to conform to qualitative research standards.

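### The stated 80% power for Cohen d=0.5 with 33 per arm cannot be reproduced from the stated inputs, and it holds or fails according to an unstated model and pre-post correlation

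*Protocol article*

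**What the plan says.** The Power Analyses section gives a "sample size of n=66 (33 in the direct group and 33 in the WLCG" arms respectively, and says that this number "is sufficient to reach a required power of at least 80% when assuming Cohen" d of 0.5. It divides 66 by 0.75 to allow for 25% dropout, obtains 88, and sets a target of 100. It adds: "This sample size will also be sufficient when adding the covariates to the model". The covariates are not named. The calculation is described only as "A power analysis in R (R Core Team) [37] (script available on request".

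The Statistical Analysis section defines the effect as a difference between BITT and WLCG. It says that "the pre, post, and follow-up changes (BITT vs WLCG) on the continuous outcomes" will be tested with mixed models. Treatment center is listed there among the moderators. The Randomization section says "we will stratify by center".

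The Study Design section has assessments at T0, T1, T2 (3 months), T3 and T4. The waitlist arm receives BITT after T2, so only T1 and T2 compare the arms before crossover.

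**The concern.** The three printed inputs (33 per arm, d=0.5, at least 80%) do not fit together for an ordinary comparison of two groups. About twice as many participants are needed for that. Some gain from baseline adjustment or repeated measures must therefore be built into the figure, and the reader cannot see which.

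This matters because the answer depends strongly on the model. The analysis wording speaks of changes. If it is carried out as a comparison of changes with T0 means left free, power at the planned size can be well under 80%. If the model conditions on T0, it need not be. A reader of a null result could not tell whether a moderate effect had been given a fair test.

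**Working it through.** **Inputs.** From Power Analyses: n=33 per arm, d=0.5, 25% dropout, target 100. Assumed because not stated: alpha 0.05, two-sided unless noted; d in units of the SD at a single time point; the same effect at T1 and T2; compound symmetry with correlation ρ between any two assessments.

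**Dropout step.** 66/0.75 = 88, which reproduces. The target of 100 leaves 75 after 25% dropout, taken as 37 per arm.

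**Plain two-group comparison.** The noncentrality is d√(n/2) = 0.5 × √16.5 = 2.03 on 64 degrees of freedom.

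| n per arm | Power, two-sided |
|---|---|
| 33 | 51.6% |
| 37 | 56.4% |
| 50 | 69.7% |
| 64 | 80.1% |

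The normal approximation at 33 per arm gives Φ(2.03 − 1.96) = 52.8%. One-sided power at 33 per arm is 64.2%. The stated 80% is not reached in any of these ways with 33 per arm.

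**What would make 33 per arm sufficient.** Let F be the variance of the analysed quantity relative to a single unadjusted score, so that the effective d is 0.5/√F. Power of 80% at 33 per arm requires F of at most 0.51.

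| Analysis | F | ρ needed for 80% at 33 per arm |
|---|---|---|
| One time point, baseline-adjusted | 1 − ρ² | about 0.70 |
| One time point, change score | 2(1 − ρ) | about 0.75 |
| Mean of T1 and T2, baseline-adjusted | (1 + ρ)/2 − ρ² | about 0.48 |
| Mean change over T1 and T2 | 1.5(1 − ρ) | about 0.66 |

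For the third row, ρ=0.5 gives F = 0.75 − 0.25 = 0.50 and power 80.8%. (Under this formula a correlation near zero also gives F of about 0.5; intermediate values give less power, with a low of 76% at ρ=0.25.)

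A paired t-test on 33 participants gives 79.5%, but that is a within-group test and not the BITT versus WLCG contrast.

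**Planned size, 37 per arm, d=0.5.**

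| ρ | One time point, change | One time point, adjusted | Mean change T1, T2 | Mean of T1, T2, adjusted |
|---|---|---|---|---|
| 0.3 | 43.4% | 60.4% | 54.4% | 80.9% |
| 0.5 | 56.4% | 68.8% | 68.8% | 85.1% |
| 0.6 | 66.0% | 75.6% | 78.2% | 89.2% |
| 0.7 | 78.2% | 84.4% | 88.5% | 94.3% |

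The factor in the last column is largest at ρ=0.25, where F = 0.625 − 0.0625 = 0.5625 and power is 80.8%. It therefore stays at about 81% or above for any non-negative ρ. The mean-change analysis reaches 80% at 37 per arm only from ρ of about 0.62.

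**Centre.** The article gives no between-centre variance, so the gain from adjusting for centre cannot be computed. Four centres cost 3 degrees of freedom.

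**The case against.** The best reply is that 52% is the power of an analysis the trial does not plan. The article refers to a model with covariates and to mixed models over repeated assessments, and the R script may well have simulated exactly that. A baseline-adjusted mean of T1 and T2 at ρ=0.5 needs 33 per arm, the number printed. This stands. A reader might infer that the trial is underpowered, or that an arithmetic error has been shown, but the document supports neither. Nor does it support quoting a detectable d of about 0.66 (unadjusted) or 0.57 (one adjusted time point, ρ=0.5) as the trial's own. With both controlled assessments and baseline adjustment at ρ=0.5, the detectable d with 37 per arm would be about 0.66 × √0.5 = 0.47.

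A second reply is that testing changes with mixed models does not mean using change scores as the dependent variable, and that covariate lists usually belong in the analysis plan. This also stands. A reader might infer that baseline and centre are left out of the main model. The article is silent rather than contrary, and a statistical analysis plan could name both. Naming centre as a moderator does not exclude it from the main model.

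These replies do not rescue the printed claim. The article makes a definite numerical statement and gives inputs that do not yield it. A script on request does not make the statement checkable.

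**Conclusion.** The point holds as a defect in the published justification: at least 80% power does not follow from 33 per arm and d=0.5 without an unstated model and correlation. The gap against a plain two-sided comparison is 80% versus 52%, or 33 versus 64 per arm.

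Whether the trial itself has 80% power is undetermined. At 37 per arm it does if the primary model conditions on T0 and uses both T1 and T2. It does not if changes averaged over T1 and T2 are compared without conditioning and ρ is below about 0.62. At ρ=0.5 that choice moves power from 69% to 85%.

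These figures rest on alpha 0.05 two-sided, compound symmetry and an equal effect at T1 and T2. The last assumption deserves care, because the waitlist arm may receive other trauma therapy after the treatment week.

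**What to change.** 1. Restate the power with the alpha, sidedness, endpoint, time point or points, model, named covariates and correlation actually used. If the calculation was a simple two-group or change comparison, replace it with the power or detectable effect for the planned analysis, shown over a range of ρ.
2. State, in the analysis plan if it is not already there, that the primary BITT versus WLCG mixed model uses the pre-crossover assessments T1 and T2, with the T0 score as covariate (or T0 means constrained equal) and centre, the stratification factor, as a fixed effect. Do this before the outcome data are analysed by arm.

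The cost is one reworded paragraph and one model statement. T0 is already collected, and with 104 participants reported as enrolled the sample size is not affected. The stated power may become less favourable. Centre uses about 3 degrees of freedom for a gain that cannot be sized from the document.

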### Participant Recruitment and Procedure

We will conduct this study in four youth care centers in the European and Caribbean Netherlands: Levvel, Karakter, Fornhese-GGz Centraal, and Mental Health Caribbean (Bonaire). Centers were eligible to participate if they had extensive experience in treating chronically traumatized children and adolescents, were trained in EMDR and TF-CBT, had experienced systemic therapists and psychomotor therapists, and had the capacity to implement the study. The therapist from the participating center will verbally inform eligible adolescents about the study and provide them with an information letter. In addition, the adolescent and their caregivers will be offered the opportunity to discuss the study with the researcher to receive more information about the study and ask questions. The researcher will discuss all referrals with an experienced child and adolescent psychiatrist with expertise in PTSD. All adolescents will provide written informed consent, and legal caregivers of adolescents aged 12-15 years will also provide consent.

### Randomization

After obtaining written informed consent from participants, an independent researcher will randomize them to either the BITT group or WLCG using computerized block-wise randomization in Castor Electronic Data Capture [38]. We will use random block sizes to avoid predictability for the researchers and we will stratify by center. The researcher completing the assessments will be blinded to the group allocation (ie, BITT vs WLC). We will explicitly instruct participants not to communicate their group allocation to the researcher.

### Treatment

#### Pretreatment

A personalized “crisis prevention plan” will be developed individually with all participants and, if applicable, their caregivers before the treatment phase. The crisis prevention plan will include the following:

Possible risk factors to consider (eg, self-harm, suicidality, alcohol and drug abuse, and aggression);Signs and tools for maintaining stability and preventing deterioration;Clear arrangements regarding whom to contact in case of emergency (eg, the main responsible clinician during working hours and local crisis service outside regular working hours) with up-to-date contact information.

Furthermore, before starting BITT, a personalized treatment plan will be developed with specific trauma targets in close collaboration with the adolescent, caregivers, and BITT therapist. The therapist will also be assigned as a personal case manager for individual adolescents throughout the BITT week. The BITT therapist will provide psychoeducation concerning PTSD symptoms and intensive treatment to adolescents and caregivers before the start of BITT.

#### The BITT

BITT consists of a 1-week (ie, 5 consecutive workdays) intensive trauma treatment with 2 daily manualized therapy sessions comprising TF-CBT (90 min) in the morning followed by EMDR (90 min) in the afternoon (ie, 10 sessions in total; 5 TF-CBT and 5 EMDR). The 90-minute session duration is based on the results of a previous pilot study into BITT for adolescents, which indicated that the burden of 90-minute sessions was evaluated as acceptable [25]. Both TF-CBT and EMDR therapy are effective and well-established treatments for children and adolescents suffering from trauma [15,39]. In both TF-CBT and EMDR, the primary objective is to address and reprocess traumatic memories and diminish the distressing emotions associated with traumatic life events. In TF-CBT, therapists apply gradual exposure from the beginning by having adolescents create a trauma narrative. Gradual exposure is applied by first telling the trauma narrative aloud, then writing it, and then reading it aloud. This also helps adolescents modify dysfunctional trauma-associated cognitions. On the last day of the BITT, the adolescent shares the trauma narrative with the caregivers during a so-called social sharing, which is a module of TF-CBT. Often this is the first time caregivers and adolescents engage in a conversation about the traumatic experience. The caregiver or caregivers are then provided with the opportunity to acknowledge the harm experienced by the adolescent, reflect on their role as a parent, and consider how they could have acted differently. This interaction is seen as an important step in trauma processing. In EMDR, the adolescent recalls the traumatic memories while simultaneously making horizontal eye movements and performing tasks with a high working memory load [40]. Therapists will use the Dutch EMDR protocol for children and adolescents [41,42].

The sequence of TF-CBT first and EMDR second is related to a proven better treatment outcome compared to the reversed sequence [43]. Experienced therapists trained in EMDR and TF-CBT will conduct all treatment sessions. Different therapists will provide sessions that conform to a so-called “therapist rotation” scheme with a maximum of 3-4 therapists per adolescent per week. Therapist rotation is applied since it seems to decrease avoidance in adolescents to engage in trauma therapy [44]. Treatment will take place in an outpatient setting.

Between therapy sessions, adolescents will participate in psychomotor therapy (PMT). PMT is a therapeutic approach in which physical movement and bodily awareness play a central role. In the morning of every BITT day, the focus during PMT will be on bodily awareness (eg, observing body signals related to PTSD) and in the afternoon, the focus will be on relaxation. Existing evidence shows that body- and movement-oriented interventions have a positive effect on diminishing PTSD symptoms [45,46].

During parental counseling, primary caregivers will receive psychoeducation, social support skill training, and social sharing (a total of 5 sessions of 90 min). Research has shown that involving caregivers is a crucial element in the treatment of children and adolescents, which contributes to fewer dropouts and increased treatment effects [39].

Adolescents will start and end the day together. PMT sessions are provided in a group setting. The TF-CBT and EMDR sessions are provided individually. Table 1 provides an overview of the therapy program.

**Table 1 table1:** Therapy program.

Time	BITT week				
	Monday	Tuesday	Wednesday	Thursday	Friday
9-9:15 AM	Start (8:45 AM)	Start	Start	Start	Start
9:15-10:15 AM	PMT^a^	PMT	PMT	PMT	PMT
10:30 AM-12 PM	TF-CBT^b^ Parental counseling^c^	TF-CBT	TF-CBT Parental counseling	TF-CBT	EMDR
12-1 PM	Break	Break	Break	Break	Break
1:15-2:45 PM	EMDR^d^	EMDR Parental counseling	EMDR	EMDR Parental counseling	Social sharing
3-3:45 PM	PMT	PMT	PMT	PMT	Closing (3-3:30 PM)
4-4:15 PM	Closing	Closing	Closing	Closing	N/A^e^

^a^ PMT: psychomotor therapy.

^b^TF-CBT: trauma-focused cognitive behavioral therapy.

^c^Caregivers receive parental counselling at the same time that the adolescent receives trauma therapy.

^d^EMDR: eye movement desensitization and reprocessing.

^e^N/A: not applicable.

### Training and Implementation

All health care professionals involved in BITT are trained by expert therapists before providing treatment, ensuring the quality of care. During this 1-day training, all modules of the BITT will be taught. In addition, the TF-CBT therapists will follow a 1-day training about the BITT-specific TF-CBT elements. Furthermore, BITT therapists from all participating centers without a TF-CBT or EMDR license will be trained by expert and licensed senior TF-CBT and EMDR supervisors from Levvel. These expert therapists were also involved in the development of the BITT program and have nationally renowned expertise. The researcher determining the PTSD symptoms during the study will be trained in the Clinician-Administered PTSD Scale for *DSM-5* (*Diagnostic and Statistical Manual of Mental Disorders* [Fifth Edition])-Child/Adolescent Version (CAPS-CA-5). During the BITT, the supervisors from Levvel will provide daily supervision to all therapists at the participating centers during a daily multidisciplinary consultation. During this consultation, all BITT therapists work closely together enhancing a clear focus on the treatment plan.

### Treatment Integrity

During the BITT, 2 supervisors from Levvel will provide daily supervision to all therapists of the participating centers in close collaboration with dedicated experts from those centers. In this way, the consistency and quality of the BITT are monitored across sites. Furthermore, therapists will complete detailed therapy checklists that will be assessed by a researcher to ensure that the treatments are delivered as intended by the protocol. In addition, therapists will record the therapy sessions with audiotapes if the participant provides permission. A total of 2 trained psychologists will independently code a random 15% of these therapy sessions to assess the treatment integrity.

### Assessment Instruments

The assessments of the primary and secondary outcomes and demographic predictor variables consist of digital questionnaires and digital or face-to-face semistructured interviews administered to both the adolescents and one of their caregivers. The measurement instrument we selected for assessing the primary outcome, namely the CAPS-CA-5, is considered the golden standard for measuring PTSD. In selecting the questionnaires, we aimed to select short surveys with adequate psychometric properties. If the participant provides permission, we will audiotape the semistructured interviews. A total of 2 trained psychologists will independently code a random 15% of these sessions to measure the interrater reliability. All questionnaires will be completed in Castor Electronic Data Capture [38]. The completion time of the assessments for adolescents varies from 75 to 120 minutes per assessment moment and for the caregiver from 30 to 65 minutes per assessment moment. The overall time for therapists to complete the assessments is 20 minutes. Table 2 provides an overview of the study parameters.

**Table 2 table2:** Study parameters.

Outcomes		Assessment instrument	T0^a^	BITT^b^	T1^c^	T2^d^	T3^e^	T4^f^
Demographics		—^g^	A^h^, C^i^	—	—	—	—	—
**Primary**								
	PTSD^j^ symptoms	CATS-2^k^	A, C	A	A, C	A, C	A, C	A, C
	Clinical diagnosis of PTSD	CAPS-CA-5^l^	A	—	A	A	A	A
**Secondary**								
	Depression symptoms	PROMIS^m^ depression	A	A	A	A	A	A
	Anxiety symptoms	PROMIS anxiety	A	A	A	A	A	A
	Anger symptoms	PROMIS anger	A	A	A	A	A	A
	Quality of life	EQ-5D-Y-3L	A, C	A	A, C	A, C	A, C	A, C
	Risk-behavior and safety	Risk behavior and safety	A	—	A	A	A	A
	Parental PTSD	PCL-5^n^ including LEC-5^o^	C	—	C	C	C	C
	Rating of sessions and therapy	ORS^p^ and SRS^q^	—	A	—	—	—	—
**Qualitative**								
	BITT^r^ experience	Qualitative interview	—	—	A, C, T^s^	A, C	—	—

^a^T0: baseline.

^b^During the BITT questionnaires are assessed daily.

^c^T1: directly after BITT or WLCG.

^d^T2: 3 months follow-up.

^e^T3: 6 months follow-up.

^f^T4: 9 months follow-up.

^g^Not applicable.

^h^A: adolescent.

^i^C: caregiver.

^j^PTSD: posttraumatic stress disorder.

^k^CATS-2: Child and Adolescent Trauma Screen.

^l^CAPS-CA-5: Clinician-Administered PTSD Scale for *DSM-5 (Diagnostic and Statistical Manual of Mental Disorders* [Fifth Edition])-Child/Adolescent Version.

^m^PROMIS: Patient-Reported Outcomes Measurement Information System.

^n^PCL-5: PTSD Checklist for *DSM-5*.

^o^LEC-5: Life Events Checklist for *DSM-5*.

^p^ORS: Child Outcome Rating Scale.

^q^SRS: Session Rating Scale.

^r^BITT: Brief Intensive Trauma Treatment.

^s^T: therapist.

